### Recruitment and Setting

We will recruit participants from gynecologic oncology practices at 3 clinic settings in Texas: 1 safety net practice located in Dallas, 1 safety net practice located in Houston, and 1 faculty group practice located in Houston. Cumulatively, the sites serve approximately 140 eligible patients per year and ensure a diverse population of 120 participants can be recruited during the 24-month recruitment period. A total of 60 participants will be randomly assigned to the intervention group and receive care using the POSTCare process, and another 60 will be randomly assigned to the control group. To be included, patients must (1) be diagnosed with ovarian cancer at the age of 18 years or older; (2) be within 3 months of completing initial treatment for stage 2-4 ovarian cancer. Treatment may include surgery, chemotherapy, radiation therapy, immunotherapy, or other biologics. Participants may be on maintenance therapy; and (3) be able to provide consent in English or Spanish. Patients who are enrolled in hospice care directly following the treatment conclusion will not be eligible for the study. It is anticipated that this study sample will reflect the ethnic and racial diversity of our clinical settings.

### Recruitment Procedures

Study research coordinators will have access to the electronic medical record at each site. They will collaborate with clinical personnel to identify patients who will be completing initial therapy. Coordinators will work to identify patients in treatment at least 8 weeks before the completion of therapy. They will identify an upcoming clinical appointment, either in clinic or infusion, where the team will approach patients to provide information about the study, answer questions they may have, and obtain informed consent. Enrolled participants will be asked to complete a web-based, self-administered survey using a smart device to collect baseline measurements before randomization.

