### Sample Size

We will enroll 120 women completing primary treatment for stage 2-4 ovarian cancer from 3 urban gynecologic oncology clinics located in the US state of Texas. Participants will have received some combination of surgery, chemotherapy, radiation therapy, and biologics. Continued maintenance therapy is not an exclusion factor. The disease-stage sample frame was developed with input from our gynecologic oncology collaborators based on treatment exposures and the similarity of survivorship challenges. Aim 1 proposes to implement a RCT devised to compare QOL measures among patients with ovarian cancer randomized to receive usual care versus the POSTCare survivorship care transition program. The Functional Assessment of Cancer Therapy-Ovarian (FACT-O) QOL survey will be collected at baseline as well as 12 and 24 weeks after the initial course of adjuvant chemotherapy. The primary end point will be the 12-week survey. The sample size of 120 patients provides at least 80% power to detect a 7% increase in the mean FACT-O score for women randomized to the POSTCare survivorship care intervention. This is sufficient to ascertain a minimally important difference of 8 points [32].

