### Randomization

After the baseline survey is administered, the biostatistician will use SAS (SAS Institute) to perform a permuted stratified blocked randomization [33]. The stratification variable used maintenance therapy versus no maintenance therapy. The rationale for this stratification is that those patients with ovarian cancer who receive maintenance therapy with a poly (ADP-ribose) polymerase (PARP) inhibitor may experience a different symptom burden or illness trajectory that impacts outcomes [3]. Survivors will be randomly allocated to either the control group or the POSTCare intervention group with a 1:1 ratio (N=120). Stratification will be based on disease stage and maintenance therapy (a PARP inhibitor vs Bevicizumab vs no maintenance). Each of these factors is associated with overall QOL and symptom burden. Participants, clinicians, data collectors, biostatisticians, and investigators will be blinded to allocation. The research nurse interventionist (described below) will not be blinded but will not conduct study activities related to measuring, collecting, or interpreting outcomes. Although this is a low-risk intervention, unblinding decisions will be made by the investigators in the context of serious adverse events attributable to the study. If a decision is made to unblind a participant, the study data coordinating center will undertake the unblinding and protect the confidentiality of treatment assignments for other participants. The treatment assignment will be communicated to the participant and the participant’s treating physician. The unblinding event will be reported to the Baylor College of Medicine institutional review board, documented in trial records, and the analysis of study outcomes may be adjusted to account for the unblinded participant to ensure that the integrity of the overall trial results is maintained. Criteria for study dropout include withdrawal of consent, failure to adhere to protocol, loss to follow-up, health changes making further participation burdensome, and personal reasons or changes in life circumstances.

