Booster survivorship navigation telephone contacts occur at 4 weeks and 8 weeks after baseline. The survivorship coaches will review health goals, including living well, adjust goals as needed, discuss progress, identify barriers, and brainstorm about strategies to overcome barriers. The survivorship coaching intervention is delivered through telehealth by the nurse survivorship navigation coach. For participants who do not have a smart device, the intervention can be delivered through a smart device provided by the study in a clinic setting.

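### Baseline and randomisation are not tied to the end of treatment, and eligibility, boosters and the primary survey are counted from different origins

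*Protocol article*

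**What the plan says.** All references are to the protocol article.

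- **Identification and consent (Recruitment Procedures).** "Coordinators will work to identify patients in treatment at least 8 weeks before the completion of therapy". Then: "They will identify an upcoming clinical appointment, either in clinic or infusion, where the team will approach patients" and take consent. No week is given for that appointment.
- **Baseline and randomisation (Recruitment Procedures; Randomization).** Enrolled women complete a "web-based, self-administered survey using a smart device to collect baseline measurements before randomization". The next step is: "After the baseline survey is administered, the biostatistician will use SAS" to allocate. Neither section links these steps to the end of treatment.
- **Eligibility (Recruitment and Setting).** A woman must be no more than 3 months from completing initial treatment; before or after is not stated. She may already be on maintenance. On hospice: "Patients who are enrolled in hospice care directly following the treatment conclusion will not be eligible for the study".
- **Strata (Randomization).** One sentence gives maintenance versus none. Another says: "Stratification will be based on disease stage and maintenance therapy (a PARP inhibitor vs Bevicizumab vs no maintenance". Neither says whether planned or started maintenance is meant.
- **Boosters (Patient-Centered Design).** "Booster survivorship navigation telephone contacts occur at 4 weeks and 8 weeks after baseline".
- **Outcome clock.** Sample Size and Outcome Measures collect FACT-O at baseline and "12 and 24 weeks after the initial course of adjuvant chemotherapy". Study Design counts the 12 weeks from the survivorship transition, and the Results part of the Abstract counts them from the intervention.

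**The concern.** The primary endpoint is a score at a fixed time, so the plan needs one origin for that time. It must be an origin that every woman has reached when she is randomised. The document instead uses the end of treatment for eligibility, the end of chemotherapy (or the transition, or the intervention) for the outcome, and baseline for the boosters. Nothing fixes how far baseline lies from the end of treatment.

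Two things are at stake. First, the amount of intervention delivered before the primary survey could vary from all of it to none, so the 12-week contrast would not describe one defined exposure. Second, a criterion that refers to events after treatment cannot be applied to a woman randomised while still on treatment. If she then entered hospice, the team would have to decide after randomisation whether she counts, and that decision would be related to prognosis and quality of life.

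**Working it through.** The plan gives no figure for the interval between baseline and the primary survey, so there is none to reproduce. The check places the stated steps on one calendar.

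**Inputs.** Primary survey at 12 weeks and later survey at 24 weeks after chemotherapy (Sample Size, Outcome Measures). Boosters at 4 and 8 weeks after baseline (Patient-Centered Design). Entry window of 3 months (Recruitment and Setting), taken as 3 × 52/12 = 13 weeks. Identification from 8 weeks before completion (Recruitment Procedures). Assumption: the end of chemotherapy is the end of treatment, called week 0.

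**Formulas.** Let *b* be the week of baseline.
- Boosters fall at *b* + 4 and *b* + 8.
- The gap from baseline to the primary survey is 12 − *b*; to the later survey it is 24 − *b*.
- The second booster falls after the primary survey when *b* + 8 > 12, that is *b* > 4.
- The first booster falls after it when *b* + 4 > 12, that is *b* > 8.
- The survey falls at or before baseline when 12 − *b* ≤ 0, that is *b* ≥ 12.

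| Baseline week *b* | Boosters at week | Weeks from baseline to primary survey | Weeks from baseline to later survey |
|---|---|---|---|
| −8 | −4 and 0 | 20 | 32 |
| 0 | 4 and 8 | 12 | 24 |
| 4 | 8 and 12 | 8 | 20 |
| 5 | 9 and 13 | 7 | 19 |
| 8 | 12 and 16 | 4 | 16 |
| 13 | 17 and 21 | −1 | 11 |

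**Reading the table.**
- The rows from 0 to 13 need only the sponsor's most favourable reading, entry after treatment. The second booster comes too late for any baseline after week 4, both come too late after week 8, and the primary survey is at or before baseline from week 12.
- The row at −8 is an extreme that the text does not rule out and does not state.
- If chemotherapy is not the last treatment, which the listed mix of modalities in Sample Size allows, the chemotherapy clock starts before treatment completion and entry shifts further to the right in the table.
- On the clock in Study Design or in the Abstract, the primary survey cannot precede baseline. The document does not say which of the clocks governs.

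**Criteria side by side.** Consent can take place at an infusion visit, so during treatment. The hospice criterion concerns what happens directly after treatment. It can be verified at randomisation only if randomisation waits, and no rule says that it does. For maintenance, the document does not say when the decision is made. A planned regimen could serve as the stratum, but the definition is not given.

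The number of women in each position cannot be computed: the document gives no distribution of entry times and no hospice rate.

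**The case against.** The strongest reply is that the 8-week sentence concerns identification only, and that the rest of the article points to entry around or after completion of treatment. Participants are described as having received their treatment and possibly being on maintenance. They are called survivors at allocation. The control visit delivers a treatment summary and surveillance schedule, and the intervention opens with a transition visit and leads up to a follow-up visit at 3 months. That stands. A reader might infer from the 8-week sentence that women are surveyed and randomised on chemotherapy; the document does not say so, only that nothing prevents it.

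Three further inferences also go too far:

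- **That strata rest on guessed maintenance.** The document does not say when maintenance is decided. Misclassified strata would in any case cost balance or efficiency; they would not bias the randomised comparison.
- **That randomised women will be dropped for entering hospice.** The text states an eligibility criterion. No section removes such women from the analysis, and the dropout criteria in Randomization do not name hospice.
- **That an on-treatment baseline weakens the adjusted analysis.** Outcome Measures does not name baseline FACT-O as an adjustment covariate.

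Variable timing also falls on both arms alike, because allocation follows the survey.

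It can be said too that the trigger for randomisation is operational detail left to a full protocol. That would excuse silence. It does not excuse stated clocks that give different dates for the same survey.

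**Conclusion.** The point holds as a conflict of time origins together with an unfixed moment of randomisation. It should be corrected.

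The firm part needs no assumption about early randomisation. With the end of chemotherapy taken as the end of treatment and all entry afterwards, the stated rules place the week-8 booster after the primary survey for baselines later than week 4, and make the survey due about 1 week before baseline for entry at 13 weeks. The 20-week interval arises only if baseline is taken 8 weeks before treatment ends, which is possible under the text but not established.

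The hospice and maintenance elements are conditional. The first bites only if a woman is randomised during treatment; the second is a missing definition. Neither the number of women affected nor any effect on the treatment estimate can be given from the document. The sample size is not in dispute here.

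**What to change.** - Allow consent during treatment, but take the baseline survey and randomise only once initial treatment is complete and hospice and maintenance status are recorded.
- State the direction of the 3-month window.
- State whether planned or started maintenance defines the stratum.
- Count the 12- and 24-week surveys from randomisation in both arms, and use that one definition in the Abstract, Study Design, Sample Size and Outcome Measures.
- State that a woman who enters hospice after randomisation is analysed as randomised.
- Reconcile the booster timing in Patient-Centered Design with the same time zero. How the contacts are scheduled is for the investigators to settle.

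The cost is a short amendment. Some women who consent during treatment will be lost before randomisation, which reduces yield but does not harm the validity of the comparison.

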### Randomization

After the baseline survey is administered, the biostatistician will use SAS (SAS Institute) to perform a permuted stratified blocked randomization [33]. The stratification variable used maintenance therapy versus no maintenance therapy. The rationale for this stratification is that those patients with ovarian cancer who receive maintenance therapy with a poly (ADP-ribose) polymerase (PARP) inhibitor may experience a different symptom burden or illness trajectory that impacts outcomes [3]. Survivors will be randomly allocated to either the control group or the POSTCare intervention group with a 1:1 ratio (N=120). Stratification will be based on disease stage and maintenance therapy (a PARP inhibitor vs Bevicizumab vs no maintenance). Each of these factors is associated with overall QOL and symptom burden. Participants, clinicians, data collectors, biostatisticians, and investigators will be blinded to allocation. The research nurse interventionist (described below) will not be blinded but will not conduct study activities related to measuring, collecting, or interpreting outcomes. Although this is a low-risk intervention, unblinding decisions will be made by the investigators in the context of serious adverse events attributable to the study. If a decision is made to unblind a participant, the study data coordinating center will undertake the unblinding and protect the confidentiality of treatment assignments for other participants. The treatment assignment will be communicated to the participant and the participant’s treating physician. The unblinding event will be reported to the Baylor College of Medicine institutional review board, documented in trial records, and the analysis of study outcomes may be adjusted to account for the unblinded participant to ensure that the integrity of the overall trial results is maintained. Criteria for study dropout include withdrawal of consent, failure to adhere to protocol, loss to follow-up, health changes making further participation burdensome, and personal reasons or changes in life circumstances.

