Ovarian cancer is a model of those cancers not typically encompassed in survivorship science and care. Over 19,000 women in the United States will receive a new diagnosis of ovarian cancer this year. For most of them, the point of diagnosis is the beginning of several years of living with cancer, treatment, and uncertainty. Most of these women will be diagnosed with advanced disease; 4 out of 5 patients have regional or advanced disease at the time of diagnosis. This contributes to the unfortunate outcomes associated with ovarian cancer, and 5-year survival rates remain below 50% despite improvements over the past 10 years. Women with ovarian cancer typically undergo treatments including surgery, chemotherapy, sometimes radiation therapy, and increasingly maintenance therapy with targeted therapies [8]. Survivorship care needs for women with ovarian cancer are unique, and frequently, their gynecologic oncology treatment program will also serve as the site of much of their cancer-focused survivorship care [9,10]. Most patients experience residual physical and psychological symptoms posttreatment [11]. Recurrence anxiety, psychosocial needs, sexual functioning, depressive symptoms, and uncertainty related to the care plan moving forward are all reported as sources of impaired well-being among ovarian cancer survivors [12-16]. Women with ovarian cancer being treated in safety net systems are more likely to have poor QOL and less likely to comply with follow-up visits, etc, making it more imperative to develop systems and processes to facilitate their survivorship transition.

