Other measures used as secondary outcomes and potential predictors were selected with a priority on acceptable psychometric performance in similar populations and acceptable performance in one of our previous studies.

“Aim 1” proposes to implement a RCT devised to compare QOL measures among patients with ovarian cancer randomized to receive usual care versus the POSTCare survivorship care transition program. Outcome measures, including the FACT-O QOL survey, the FCR-7 survey, and the PHQ-9, will be collected at baseline as well as 12 and 24 weeks after the initial course of adjuvant chemotherapy. The primary end point will consist of the 12-week FACT-O survey. The sample size of 120 patients provides at least 80% power to detect a 7% increase in the mean FACT-O score for women randomized to the POSTCare survivorship care intervention. This is sufficient to ascertain a minimally important difference of 8 points. Secondary outcomes (Table 1) will also be assessed at 12 and 24 weeks. Baseline descriptive statistics will be presented by site. Longitudinal analysis of the FACT-O QOL scores will use a mixed effects linear model with a restricted maximum likelihood estimation method, and an unstructured covariance matrix will be used to estimate trends. An interaction between intervention and time will be estimated to explore the effectiveness of POSTCare for time-varying trends [49]. Though the mixed effect model can accommodate some degree of missing data under the ignorability assumption, we also plan to use multiple imputations using the random forest method [50,51] to accommodate missing data (if greater than 10% of survey items), which will be assumed to be missing at random. In the event of a sign of a violation of that assumption, a pattern mixture model will be used to mitigate the effect of informative missingness. Secondary analyses will evaluate relationships between baseline and 12-week FACT-O scores and clinical end points progression-free survival (PFS) and overall survival (OS). Cox proportional hazard models will be used to estimate the relative risk of PFS and death per increase in FACT-O [52]. Ties in failure times will be handled with the approximate likelihood of Efron. PFS and OS will be measured from the date of randomization. PFS is defined as the minimum amount of time until clinical progression, death, or the date of last contact. OS is the duration from randomization to death or to the date of last contact (right-censoring). As is customary, secondary analyses are not powered but may help generate additional evidence that needs to be tested in the future by a properly powered study.

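### Two incompatible stratification schemes are stated, and the article ties neither the strata nor a baseline-adjusted week-12 arm difference to the primary FACT-O analysis

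*Protocol article*

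**What the plan says.** The Randomization section says the biostatistician will "perform a permuted stratified blocked randomization" after the baseline survey, allocating 120 women 1:1. It then describes the strata twice.

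- First: "The stratification variable used maintenance therapy versus no maintenance therapy". The reason given is that women on a PARP inhibitor may have a different symptom burden or illness course.
- Then, a few sentences later: "Stratification will be based on disease stage and maintenance therapy (a PARP inhibitor vs Bevicizumab vs no maintenance". It adds: "Each of these factors is associated with overall QOL and symptom burden".

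The inclusion criteria under Recruitment and Setting admit women who must "be within 3 months of completing initial treatment for stage 2-4 ovarian cancer", so disease stage has up to three levels.

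Outcome Measures sets FACT-O at 12 weeks as the primary end point. It describes a linear mixed model fitted by restricted maximum likelihood with an unstructured covariance, as a means of estimating trends. On the treatment effect it says: "An interaction between intervention and time will be estimated to explore the effectiveness of POSTCare for time-varying trends". It gives no list of covariates. FACT-O is measured at baseline, 12 weeks and 24 weeks.

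**The concern.** The two descriptions cannot both be true. Stage is a factor in one and absent from the other. Bevacizumab is pooled with PARP inhibitors in one and separate in the other. The Results section says data collection began in November 2023, so one scheme is presumably in use, and a reader cannot tell which.

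This matters for the analysis. Stratified blocks balance the arms on prognostic factors, which reduces the true variance of the arm difference. An analysis without those factors does not credit that reduction, so its standard error is too large. The terms to include cannot be written down until the scheme is known.

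The primary test is also loosely fixed. The end point is a week-12 difference, but the described model concerns trends and its interaction is exploratory. How baseline FACT-O enters the week-12 comparison affects precision and is not stated.

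**Working it through.** **1. The two schemes.** Average stratum size with N = 120:

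| Scheme | Strata | Women per stratum |
|---|---|---|
| Maintenance yes/no | 2 | 120/2 = 60 |
| Stage in two groups × three-level maintenance | 2 × 3 = 6 | 120/6 = 20 |
| Stages 2, 3, 4 × three-level maintenance | 3 × 3 = 9 | 120/9 = 13.3 |

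No other section says which applies. The Discussion mentions that recruitment and budget limit the ability to stratify, but does not name a scheme.

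**2. The plan's own power figure.** The article claims at least 80% power with 120 women for a 7% increase, and cites a difference of 8 points (which implies a mean of 8/0.07 = 114.3). It gives no SD, alpha or sidedness, so the 80% cannot be reproduced directly. Solving for the SD with 60 per arm:

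SD = 8 / [(z for alpha + 0.8416) × √(2/60)]

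- Two-sided 5%: 8 / (2.8016 × 0.18257) = 15.6
- One-sided 5%: 8 / (2.4865 × 0.18257) = 17.6

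SD 15.6 is used below because it is the two-sided value at which an unadjusted comparison just reaches the stated power.

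**3. Leaving out the strata.** Let R² be the share of FACT-O variance that the strata explain (not given; 5% to 30% assumed). With perfect balance, the true variance of the arm difference is (1 − R²) times what an unadjusted analysis estimates. The actual type I error is then 2 × [1 − Φ(1.96/√(1 − R²))], which is 4.4%, 3.9%, 2.8% and 1.9% for R² of 5%, 10%, 20% and 30%.

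A simulation allows for incomplete blocks: 4,000 trials per setting, N = 120, nine strata, blocks of 4, SD 15.6, true difference 0 or 8. Further assumptions are additive stratum effects, stage shares of 15/60/25% and maintenance shares of 40/20/40%.

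| R² | Type I: no strata | Type I: stage + three-level maintenance | Power: no strata | Power: stage + three-level maintenance | Power lost (points) |
|---|---|---|---|---|---|
| 5% | 3.9% | 4.2% | 79.8% | 81.4% | 1.6 |
| 10% | 4.1% | 5.2% | 79.7% | 82.5% | 2.8 |
| 20% | 3.1% | 5.1% | 82.8% | 88.3% | 5.5 |
| 30% | 2.3% | 4.6% | 84.5% | 92.2% | 7.7 |

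Monte Carlo standard error is √(0.05 × 0.95/4000) = 0.3 points for type I error and √(0.8 × 0.2/4000) = 0.6 points for power, so the 5% row shows little. Without the strata, 95% intervals cover about 95% to 98%. If randomisation used the nine strata but the model used only the two-level factor, the result falls in between: at R² = 30%, type I error is 3.3% and power 88.1%.

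**4. Use of baseline.** Let r be the correlation of baseline with week-12 FACT-O (not given), with equal SDs and complete data. In units of the raw week-12 contrast, the variances are:

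- raw week-12 contrast: 1
- change score: 2(1 − r)
- baseline-adjusted: 1 − r²

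Adjusted over change score is therefore (1 − r²)/[2(1 − r)] = (1 + r)/2. With separate baseline means per arm and complete data, the week-12 contrast from an unstructured model is the raw one, and the week-12 interaction is the change score. Power = Φ(8/SE − 1.96), where SE is 15.6 × √(2/60) = 2.848 times the square root of the variance above:

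| r (assumed) | Adjusted / raw | Adjusted / change | Power: raw | Power: change | Power: adjusted |
|---|---|---|---|---|---|
| 0.3 | 0.91 | 0.65 | 80.2% | 66.1% | 83.8% |
| 0.5 | 0.75 | 0.75 | 80.2% | 80.2% | 90.0% |
| 0.7 | 0.51 | 0.85 | 80.2% | 95.2% | 97.6% |

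The variance ratios do not depend on the SD. The powers do, and if the stated 80% already assumed baseline adjustment, the raw SD could be larger.

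**The case against.** The strongest reply is that most of this rests on silence. The article does not say that strata or baseline are left out. It gives no covariate list and does not say whether baseline means are constrained, and a condensed article commonly leaves such details to the full protocol or analysis plan. That stands: a reader might infer that the model is known to omit these terms, and the documents do not show it.

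A reader might also infer that the interaction is the primary test. The wording calls it exploratory and sets the week-12 end point separately. The described model can yield a week-12 contrast that uses baseline, depending on how baseline is specified. What remains is that the contrast is not named.

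A third tempting inference is that site must be in the model for valid standard errors, because the Introduction says "Women with ovarian cancer being treated in safety net systems are more likely to have poor QOL". Site is a stratum in neither scheme, so the stratified-randomisation argument does not reach it. The sentence is background on safety-net care in general, and adding site would be a precision choice.

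Nor is there a false-positive risk. Omitting strata makes the test conservative, and unadjusted power in the simulation stays at about 80% or above, so what is lost is power that the stratification could have bought.

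Finally, the second stratification sentence might be read as a fuller version of the first. That fails: the first names a single variable and has no place for stage.

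**Conclusion.** The contradiction in the Randomization section is certain, needs no assumption, and has to be reconciled. The analysis point holds in a limited form: the article calls the strata prognostic for quality of life, does not say that they enter the model, and does not name the week-12 arm difference as the primary estimate.

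The size is conditional. If the strata were omitted, type I error would be about 4% down to 2% and about 2 to 8 points of power would be lost, for R² of 5% to 30% with blocks of 4. If baseline means were unconstrained, the baseline-adjusted variance would be (1 − r²) of the raw contrast and (1 + r)/2 of the change score. The article gives neither R² nor r. The change should be made, but nothing here threatens the validity of a positive result.

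**What to change.** - **Randomization:** state the one scheme actually programmed, including how disease stage is grouped, and delete the other sentence.
- **Outcome Measures:** name the primary estimate as the POSTCare minus control difference in FACT-O at week 12 from the same mixed model. Either constrain the baseline means to be equal across arms or enter baseline FACT-O as a covariate. Include fixed effects for the randomisation strata actually used.
- **Secondary:** keep the treatment-by-time interaction and the 24-week contrast.

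If the full protocol or analysis plan already specifies these terms, it is enough to check that they match the scheme in use and to say so. The cost is wording and a few degrees of freedom. With nine strata of about 13 women, some will be sparse, and stage and maintenance may need to enter as main effects: 2 + 2 = 4 degrees of freedom, against 8 for separate strata. The variables are already collected.
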